# Changes in Gut Microbiome Following Acupuncture and Moxibustion in Patients With Parkinson Disease: Protocol for a Single-Group, Prospective, Observational Study

**DOI:** 10.2196/76551

**Published:** 2025-10-29

**Keywords:** neurodegenerative disorders, gut-brain axis, microbial dysbiosis, motor and nonmotor symptoms, complementary medicine

## Abstract

**Background:**

Parkinson disease (PD), a prevalent neurodegenerative disorder characterized by motor and nonmotor symptoms, is becoming increasingly prevalent worldwide. Conventional treatment for PD involves dopamine therapy, including levodopa; however, this treatment is ineffective for nonmotor symptoms and may cause adverse effects. The gut-brain axis has been hypothesized to promote PD, and regulation of gut microbiome, which modulates the gut-brain axis, is emerging as a treatment target. Acupuncture and moxibustion exert therapeutic effects on PD and modulate the gut microbial composition.

**Objective:**

We present a protocol for analyzing the effects of acupuncture and moxibustion on gut microbiome and exploring its association with symptoms in patients with PD.

**Methods:**

This single-group, prospective, observational study will recruit 60 patients with idiopathic PD and 20 healthy participants. Baseline gut microbiome patterns and motor and nonmotor symptoms of both groups will be compared. Patients with PD will be treated with acupuncture, moxibustion, and intradermal acupuncture twice a week for 12 weeks (24 sessions total). Motor and nonmotor symptoms and gut microbiome changes in patients with PD will be compared before starting treatment (day 0), during treatment (6 weeks), at the end of treatment (12 weeks), and 2 months after the end of treatment (20 weeks). The correlation between motor and nonmotor symptoms of PD changed by acupuncture and moxibustion treatment and changes in gut microbiome will be analyzed. Healthy participants will be assessed for motor and nonmotor symptoms of PD and gut microbiome after screening.

**Results:**

This study was supported by the National Research Foundation of Korea, funded by the Ministry of Science and ICT (Information and Communication Technology), Republic of Korea, and recruitment for the study started on October 21, 2021. As of February 19, 2025, recruitment and observation ended, and data analysis is being conducted.

**Conclusions:**

This is the first clinical study to assess the effects of acupuncture and moxibustion on gut microbiome and explore its association with symptoms in patients with PD. The results will provide clinical evidence to explain the microbiome-gut-brain axis mechanism of acupuncture and moxibustion for PD and suggest the possibility of acupuncture as an alternative therapy for PD.

**Trial Registration:**

Clinical Research Information Service KCT0006669; https://tinyurl.com/42jsxs5a

**International Registered Report Identifier (IRRID):**

DERR1-10.2196/76551

## Introduction

Parkinson disease (PD) is the second most common neurodegenerative disorder [1], and its incidence has increased drastically worldwide over the past few decades, placing it as one of the most rapidly expanding neurological disorders worldwide [2,3]. The rapid growth of PD is influenced by global aging, as the prevalence of PD increases with age [4]. Therefore, the development of treatment strategies for patients with PD is expected to become increasingly important.

PD is characterized by motor symptoms such as tremor, rigidity, bradykinesia, and postural instability due to altered aggregation of α-synuclein in the brain structures termed Lewy bodies, as well as by early prominent death of dopaminergic neurons in the substantia nigra [5]. However, PD is not only characterized by motor symptoms but also by nonmotor symptoms such as constipation, depression, anxiety, anosmia, pain, and sleep behavior disorder, which have been found to occur in the prodromal phase before the onset of motor symptoms, contributing to the decreased quality of life in affected patients [6]. Based on this knowledge, a study has recently suggested that PD should be approached as a systemic disease, rather than simply as a movement disorder caused by brain dysfunction [7].

Levodopa symptomatic therapy based on conventional brain pathology is the current mainstay of PD treatment [8]. However, nonmotor symptoms are known to be unresponsive to levodopa [9], and excessive and prolonged therapy is associated with a risk of adverse events, such as dopamine dysregulation syndrome [10] and levodopa-induced dyskinesia [11]. Therefore, current treatments that target the brain alone are unlikely to be effective in treating PD, indicating the need for alternative treatments.

The gut-brain axis theory posits that the gut and brain communicate bidirectionally with each other via the blood and vagus/sympathetic nerves to regulate various human physiological and pathological functions, and the gut microbiome is gaining attention as a potential modulator of the gut-brain axis [12]. As the highly complex relationship between the gut and brain in PD has been recognized, the role of gut microbiome as a modulator of PD has also been highlighted [13].

In Traditional East Asian Medicine (TEAM), both acupuncture and moxibustion have a long history of clinical use in the treatment of PD. Recently, there has been a growing demand for complementary and alternative medicine (CAM) for PD worldwide, to compensate for the limitations of conventional PD treatments, with acupuncture playing a large role [14]. In a previous review, acupuncture and moxibustion were reported to be superior to dopamine monotherapy in improving motor and nonmotor symptoms and managing long-term symptoms in PD [15]. In another study [16], the addition of acupuncture to dopamine replacement therapy was associated with significantly superior Unified Parkinson's Disease Rating Scale (UPDRS) I-IV score improvements compared with those noted with dopamine replacement therapy alone.

Recent experimental studies have shown that acupuncture modulates the gut microbial composition [17,18]. Based on this evidence, a study using an in vivo PD model reported that GB34 and ST36 acupuncture enhanced motor symptoms and dopamine neuron protection by modulating gut microbial dysbiosis and inhibiting neuroinflammation [19]. This suggests that the effects of acupuncture may also be mediated by modulating the gut-brain axis through gut microbiome regulation. However, all studies conducted in this field to date have been experimental, highlighting the need to explore the effects of acupuncture and moxibustion on gut microbiome and explore its association with clinical symptom improvement in patients with PD.

Herein, we present a protocol for a study analyzing the effects of acupuncture and moxibustion on the gut microbiome and exploring its association with symptoms in patients with PD. This study will provide new clinical evidence on the mechanisms of PD treatment with acupuncture and moxibustion, thereby increasing the level of evidence for acupuncture and moxibustion as alternative treatment methods for PD.

## Methods

### Study Design

This protocol describes a single-group, prospective, observational study aiming to analyze differences in gut microbiome between patients with idiopathic PD and healthy participants, to observe changes in gut microbiome after 12 weeks of acupuncture and moxibustion in patients with PD, and to correlate these changes with changes in motor and nonmotor symptoms of PD that were altered by acupuncture and moxibustion treatment. The gut microbiome patterns at baseline in healthy participants and screened patients with PD will be analyzed to determine whether the gut microbiome of patients with PD is different from that of healthy participants. Patients with PD will be treated with acupuncture, moxibustion, and intradermal acupuncture twice a week for 12 weeks, yielding a total of 24 sessions. The motor and nonmotor symptoms of PD and gut microbiome changes in response to acupuncture and moxibustion will be compared before starting treatment (day 0), during treatment (6 weeks), at the end of treatment (12 weeks), and 2 months after the end of treatment (20 weeks). The correlation between motor and nonmotor symptoms of PD changed by acupuncture and moxibustion treatment and changes in gut microbiome will be analyzed. The enrollment, interventions, and assessments of patients with PD are summarized in Table S1 in Multimedia Appendix 1. A schematic of the study process is shown in Figure 1. Healthy participants will be assessed for motor and nonmotor symptoms of PD and gut microbiome after screening. The enrollment and assessment of healthy participants are summarized in Table 1. Kyung Hee University Korean Medicine Hospital, Seoul, Republic of Korea, will serve as the study site. The study protocol was registered with the Clinical Research Information Service (KCT0006669) on October 15, 2021. This protocol was reported in accordance with the SPIRIT (Standard Protocol Items: Recommendations for Interventional Trials) guidelines (Multimedia Appendix 2).

**Figure 1 figure1:**
[figure not shown]
Flowchart of the study process. BBS: Berg Balance Scale; BSS: Bristol Stool Scale; GSRS: Gastrointestinal Symptom Rating Scale; MDS-UPDRS: Movement Disorder Society–Sponsored Revision of the Unified Parkinson's Disease Rating Scale; MYMOP: Measure Yourself Medical Outcome Profile; PD: Parkinson disease; PDQ-39: 39-Item Parkinson's Disease Questionnaire; S&E: Schwab and England Activities of Daily Living Scale; TDS: Total Dyspepsia Symptom Scale; TUG: Timed Up and Go Test.

**Table 1 table1:** Schedule for the enrollment, interventions, and assessments of healthy participants.

Visit	0	1
Day	–14 to 0	0
Week	0	1
Visit window	—	±7
Informed consent	✓	
Demographic information	✓	
Medical history	✓	
Medications investigation	✓	
Vital sign	✓	
Hoehn and Yahr stage	✓	
Evaluating inclusion and exclusion criteria	✓	
MDS-UPDRS^a^		✓
BBS^b^		✓
TUG^c^		✓
S&E^d^		✓
PDQ-39^e^		✓
Blood sampling^f^		✓
Fecal sampling^g^		✓
Abdominal examination		✓
GSRS^h^		✓
TDS^i^		✓
BSS^j^		✓
MYMOP^k^		✓
Korean medicine doctor interview		✓

^a^MDS-UPDRS: Movement Disorder Society–Sponsored Revision of the Unified Parkinson's Disease Rating Scale.

^b^BBS: Berg Balance Scale.

^c^TUG: Timed Up and Go Test.

^d^S&E: Schwab and England Activities of Daily Living Scale.

^e^PDQ-39: 39-Item Parkinson's Disease Questionnaire.

^f^Analyzing gut microbiome–related metabolites.

^g^Analyzing gut microbiome.

^h^GSRS: Gastrointestinal Symptom Rating Scale.

^i^TDS: Total Dyspepsia Symptom Scale.

^j^BSS: Bristol Stool Scale.

^k^MYMOP: Measure Yourself Medical Outcome Profile.

### Eligibility

Inclusion and exclusion criteria for patients with PD are summarized in Textbox 1.

Since patients with early-stage PD typically show a good response to anti-Parkinson agents such as levodopa [20], it is challenging to isolate and evaluate the additional effects of acupuncture and moxibustion in this population. Therefore, this study included patients who have been taking anti-Parkinson agents for more than 5 years or who were at Hoehn and Yahr stage 2-3, representing the midstage or beyond. Inclusion and exclusion criteria for healthy participants are summarized in Textbox 2.

Dropout criteria are summarized in Textbox 3.

Inclusion and exclusion criteria for patients with Parkinson disease (PD).
**Inclusion criteria**
Men and women aged 50-85 yearsPatients with idiopathic PD who have been taking anti-Parkinson agents (excluding anticholinergic drugs) for >5 yearsHoehn and Yahr stage 2-3Patients who have no cause of cognitive or motor impairment other than PDPatients who have voluntarily agreed to participatePatients who have not participated in other clinical trials within the last 1 month
**Exclusion criteria**
Patients diagnosed with secondary Parkinsonism or atypical Parkinsonian syndromeConsumption of oral antibiotics that may affect results within the past monthLoss of consciousness for more than an hour due to head traumaPatients with severe vision or hearing problemConsumption of probiotics that may affect results within the past monthConsumption of medication (such as analgesics, anti-inflammatory drugs, or antibiotics) that may affect the gastrointestinal system within a week from the time of fecal samplingHistory of severe heart disease (eg, myocardial infarction or heart failure)Patients with a medical history of neurosurgical procedure (eg, deep brain stimulation)Patients who have been diagnosed with cancer or treated for cancerPatients with glaucomaChronic alcohol consumption or drug abuseWomen who are pregnant or breastfeedingPatients with diseases such as coagulation disorders that cannot be treated with acupuncturePatients with clinically significant psychiatric symptoms or medical diseasesParticipants who are judged by the investigator to have nonconformity for participation in the trial for any reason

Inclusion and exclusion criteria for healthy participants.
**Inclusion criteria**
Men and women aged 50-85 yearsParticipants who have no problems with cognitive function and who have voluntarily agreed to participate in the study through written consentParticipants who selected to match the “Patients with PD” group with age, sex, and other health conditions, excluding the diagnosis of Parkinson disease (PD)
**Exclusion criteria**
Participants diagnosed with PDParticipants who have taken oral antibiotics within the past 1 month, as it was assumed that this medication could affect the results of this studyParticipants with a history of loss of consciousness for more than 1 hour due to brain traumaParticipants with vision or hearing problems to the extent that the examination cannot proceed smoothlyParticipants who have consumed health functional food such as Lactobacillus within the last 1 month, as it is assumed that this health functional food could affect the results of this studyParticipants who took medications that could affect the gastrointestinal tract, such as pain relievers, anti-inflammatory drugs, and antibiotics, within 1 week of stool collectionParticipants with a history of serious heart disease such as myocardial infarction or heart failureParticipants with a history of malignant tumorParticipants with a history of glaucomaParticipants with a history of chronic alcohol or substance abuseParticipants with clinically significant psychiatric symptoms or medical conditionsAny participant that the investigator judged to be physically or mentally inappropriate to participate in the clinical trial based on other laboratory findings

Dropout criteria.
**Dropout criteria**
Participants who do not comply with the study physician's instructionsParticipants who have taken other medications that may affect the results of the study without the consent of the study physicianPatients who have developed other secondary infections and disease conditions that may affect Parkinson disease symptomsParticipants who have withdrawn consent or requested discontinuation of treatment

### Recruitment

For the study, 20 healthy participants and 60 patients with PD will be recruited through walk-ins or hospital and school bulletin boards, public transportation billboards, newsletters, and other online advertisements. Participants who wish to participate will receive an explanation of the consent form, provide written consent of their own free will, and participate in the study if the researcher determines that they are suitable through a screening process. The screening items are as follows: demographic information, medical history, PD diagnosis, treatment history, medications, vital signs, Hoehn and Yahr stage assessment, and inclusion and exclusion criteria evaluation (Table S1 in Multimedia Appendix 1 and Table 1 on code rather than the participant's name.

### Interventions

All patients with PD will receive acupuncture, moxibustion, and intradermal acupuncture treatments twice a week for 12 weeks, for a total of 24 sessions.

#### Acupuncture Treatment

Acupuncture treatment for patients with PD will be performed by a Korean medicine doctor specializing in internal medicine of Korean medicine or by a Korean medicine doctor with at least 2 years of clinical experience in the field under the supervision of a specialist, using disposable sterile acupuncture (Dongbang Acupuncture, Co, Ltd) with a thickness of 0.25 mm and a length of 30 or 40 mm. The acupuncture points will be 12 basic acupuncture points and 36 additional acupuncture points selected according to the relevant nonmotor symptoms (Table 2). A total of 25 points or more on both sides will be chosen. After inserting the needle vertically approximately 5-30 mm deep into each point and inducing qi with twirling for 10-15 seconds, the needle will be retained for 15 minutes and removed. All acupunctur*e* treatments will be performed in compliance with the STRICTA (Standards for Reporting Interventions in Clinical Trials of Acupuncture) guidelines [21].

**Table 2 table2:** Acupuncture points planned for use in patients with Parkinson disease.

Type	Acupuncture points
Basic acupuncture points	Bai hui (GV20), bilateral Fengchi (GB20) Upper limb: Hegu (LI4), Zhongzhu (TE3), Quchi (LI11), Shousanli (LI10), Waiguan (TE5) Lower limb: Yanglingquan (GB34), Zusanli (ST36), Xuanzhong (GB39), Taichong (LR3), Zulinqi (GB41) Auricular acupuncture: Shenmen
Additional acupuncture points selected according to nonmotor symptoms	Constipation: Bilateral Tianshu (ST25), Yanggu (SI5), Yangxi (LI5) Frequent urination, dysuria, sexual dysfunction: Jingqu (LU8), Taibai (SP3), Taixi (KI3), Fuliu (KI7) Sialorrhea: Shaofu (HT8), Dadu (SP2), Dadun (LR1), Yinbai (SP1) Dysgeusia, dysosmia: Shangxing (GV23), bilateral Yingxiang (LI20) Pain: Ouch point Sleep disorder: Neiguan (PC6), Shenmen (HT7), Zhaohai (KI6), Shenmai (BL62) Anxiety, depression: Jingqu (LU8), Zhongfeng (LR4), Yingu (KI10), Ququan (LR8) Fatigue: Qihai (CV6), Guanyuan (CV4), Zhongji (CV3) (moxibustion) Cognitive impairment: Shishencong Dysphagia: Chengjiang (CV24), Lianquan (CV23), Danzhong (CV17) Dyspepsia: Zhongwan (CV12), Gongsun (SP4) Dizziness: Neiguan (PC6), Shenmun (HT7), Lieque (LU7) Fenglong (ST40), Taibai (SP3)

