### Sample Size

This study is not intended to statistically validate the intervention effect of acupuncture and moxibustion on PD but was rather conducted as an exploratory study comparing gut microbiome markers in patients with PD and healthy participants and the effects of acupuncture and moxibustion on the gut microbiome in patients with PD. Therefore, the sample size required for the study will be 60 patients with PD and 20 healthy individuals, depending on the financial resources and study environment, and in consultation with experts in gut microbiology.

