### Statistical Analysis

#### Overview of Statistical Analysis

SPSS (ver 21.0, IBM SPSS Statistics for Windows) will be used for analysis. All measures will be presented as mean (SD) for continuous variables and as n (%) for dichotomous variables. For efficacy endpoints, the amount of change or rate of change from baseline to end of treatment and follow-up will be calculated.

All data obtained from participants will be analyzed in 2 forms: intention-to-treat (ITT) analysis and per-protocol (PP) analysis. The ITT analysis will be performed on all participants who undergo acupuncture and moxibustion at least once. For missing data on the evaluation variables, the last observation carried forward (LOCF) method will be applied. PP analysis will further be performed on participants who completed the entire study. The evaluation will be based on the results of the ITT analysis and is presented with reference to the PP analysis.

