#### Changes in Gut Microbiome–Related Metabolites and Gut Microbiome

Differences in microbiome at each time point will be measured using weighted-unweighted UniFrac distance metrics and subsequently tested using analysis of similarity (ANOSIM). Correlations of clinical outcomes and treatment effects with key microbiomes will be analyzed using Spearman rank correlation analysis, with *P*<.05 considered significant. Principal component analysis will be applied to analyze metabolite distribution in the sample. Partial least squares-discriminant analysis will be applied to identify differences between patients with PD and healthy participants when analyzing metabolite distributions. Selected gut microbiome and metabolite changes will be analyzed by 1-way repeated measures ANOVA, with significant differences between time points determined at *P*<.05. The pathway analysis or enrichment analysis will be performed to analyze the metabolic pathways of the selected metabolites. The Kyoto Encyclopedia of Genes and Genomes database [39] will be used to identify interactions between metabolites. Receiver operating characteristic analysis will be conducted to confirm whether the selected metabolites reflect the representativeness of the disease or treatment.

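### The unadjusted symptom–microbiome correlation cannot separate a gut-brain link from differences between patients in treatment content and baseline nonmotor burden

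*Protocol article*

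**What the plan says.** Some of the treatment is common to all patients. Under Interventions: "All patients with PD will receive acupuncture, moxibustion, and intradermal acupuncture treatments twice a week for 12 weeks, for a total of 24 sessions". Under Acupuncture Treatment, "the needle will be retained for 15 minutes and removed". The basic points, the press-needle sites and the electric moxibustion sites are also common to everyone.

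The rest depends on the patient: "The acupuncture points will be 12 basic acupuncture points and 36 additional acupuncture points selected according to the relevant nonmotor symptoms". Table 2 lists the additional points under 12 symptom groups. The rule on the total is a minimum without a maximum: "A total of 25 points or more on both sides will be chosen".

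Attendance can differ too. Overview of Statistical Analysis defines the main set as follows: "The ITT analysis will be performed on all participants who undergo acupuncture and moxibustion at least once".

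The link analysis is given under Changes in Gut Microbiome–Related Metabolites and Gut Microbiome: "Correlations of clinical outcomes and treatment effects with key microbiomes will be analyzed using Spearman rank correlation analysis", with significance at P<.05. No partial correlation, stratification or covariate is named. The limitations in the Discussion cover the missing PD control group, lack of blinding, diet and levodopa dose. They do not mention that acupuncture content varies with symptoms.

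**The concern.** The additional points follow complaints that the outcomes also score. Constipation and dyspepsia each bring their own points, and the GSRS, TDS and BSS measure those complaints. Part I of the MDS-UPDRS, the primary outcome, measures nonmotor experiences generally. A patient with a heavier nonmotor burden at day 0 therefore tends to differ in treatment content, in room for symptom change (including regression to the mean), and possibly in how the gut flora changes.

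If treatment intensity or severity influences both changes by separate routes, the two changes will correlate across patients with no connection between them. A rank correlation without covariates cannot tell this from a genuine link. The Discussion hypothesizes that acupuncture alters the microbiome and so improves symptoms, and the Conclusions of the Abstract expect results that help explain a microbiome-gut-brain mechanism. Two parallel, unconnected effects could then be read as support for that pathway.

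**Working it through.** **1. Does treatment content vary with symptoms?** The 12 symptom groups in Table 2 hold 3 + 4 + 4 + 2 + 1 + 4 + 4 + 3 + 1 + 3 + 2 + 5 = 36 entries, which reproduces the stated 36. LU8, SP3, PC6 and HT7 each appear twice, so 36 − 4 = 32 are distinct. The 12 basic points needled on both sides give 1 (GV20) + 11 × 2 = 23 needles, or 24 to 25 with auricular Shenmen. The floor of 25 is thus close to the basic set alone, and symptom-selected points come largely on top. If every point listed for a symptom were used, on both sides where paired, the mean would be about 30 needles for one symptom and 45 for four. That is an upper reading: the text does not require every listed point, and the fatigue entry is marked as moxibustion.

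**2. Do sessions vary?** Planned sessions are 24 for all. The analysis set needs only one treatment, so sessions received can run from 1 to 24.

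**3. What can a shared factor do to the named test?** The sample size is given as: "the sample size required for the study will be 60 patients with PD and 20 healthy individuals, depending on the financial resources and study environment". It was set by feasibility, so there is no power figure to reproduce. I take n = 60 and two-sided P<.05.

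- Critical value: t(0.975; 58 df) = 2.002, so |rho| = 2.002 / √(58 + 2.002²) = 0.254.
- Assumption, not in the documents: a factor D correlates a with symptom change X and a with microbiome change Y, and X and Y are independent given D. The induced correlation is a × a, for example 0.5 × 0.5 = 0.25 on the normal scale, or about 0.24 as a mean Spearman rho.
- Partial Spearman: rho(XY·D) = [rho(XY) − rho(XD) rho(YD)] / √[(1 − rho(XD)²)(1 − rho(YD)²)], tested on n − 3 = 57 df.

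Share of 20,000 simulated studies with P<.05 and no direct link:

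| a | Unadjusted | Adjusted for D |
|---|---|---|
| 0 | 4.8% | 4.8% |
| 0.2 | 6.0% | 5.1% |
| 0.3 | 10.3% | 5.0% |
| 0.4 | 21.3% | 5.1% |
| 0.5 | 44.9% | 5.3% |

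With D built from needle counts in Table 2 instead of a normal variable, the unadjusted rate was 9% at a = 0.3 and 48% at a = 0.5, and about 5% after adjustment.

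**4. Is adjusting for point count enough?** The return to 5% above is built in, because D itself was adjusted for. Suppose instead that baseline severity is the common cause and point count tracks it at 0.7. Adjusting for count alone then leaves about 10% at a = 0.4 and 19% at a = 0.5. Baseline burden has to be in the adjustment set.

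**5. What does adjustment cost if the link is real?** Suppose dose correlates 0.5 with microbiome change, microbiome change correlates 0.4 with symptom change, and dose acts only through the microbiome. Dose then correlates 0.5 × 0.4 = 0.2 with symptom change. The partial correlation is (0.4 − 0.2 × 0.5) / √[(1 − 0.04)(1 − 0.25)] = 0.30 / 0.849 = 0.35 instead of 0.40, and simulated power falls from 86% to 75%.

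**The case against.** Several counter-arguments have force.

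- **The size is assumed.** Nothing in the article shows that needle count or severity correlates with either change, let alone with both. At 0.2 the inflation is negligible. This stands, and the 45% must not be read as an estimate.
- **More symptoms, more needles is an inference.** Points are selected, not all mandatory, and four are shared between groups. This stands as to degree. That content differs by symptom is stated outright.
- **Abdominal stimulation is largely common.** A reader might infer from Table 2 that patients with gut complaints alone are stimulated at ST25, CV12, CV6 and CV4. Electric Moxibustion Treatment applies heat at all four in every patient, so the contrast in site is blunted. Needle number and other sites still differ.
- **The correlation is not the only evidence.** A reader might infer that the mechanism rests on this test alone. The article also plans fecal microbiome transplantation to study response to treatment, and ROC analysis of metabolites. The Spearman correlation is the statistical test specified for relating clinical outcomes to the microbiome, not the sole source of evidence.
- **The study is exploratory and admits weak causal inference.** True, and the text speaks of exploring an association. But the limitations do not name this source of confounding, and a PD control group alone would not remove it, since the variation is among treated patients.
- **Covariates may be in a fuller plan.** Possible. The article nevertheless names a specific method that, as stated, has no place for them.

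**Conclusion.** The point holds in a limited form. By design, treatment content follows baseline nonmotor symptoms, and sessions received can vary in the main analysis set. The unadjusted Spearman correlation can therefore reflect shared treatment intensity or severity rather than a gut-brain link. At n = 60 the false-link rate is about 6%, 10%, 21% or 45% for assumed correlations of 0.2, 0.3, 0.4 or 0.5 with both changes. It matters only from about 0.3 upward, and the true value is unknown.

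The documents do not support the stronger reading that a significant correlation here would be spurious, or that needle count is the established common cause. Count and severity are intertwined, and neither has been shown to drive both changes. This is a worthwhile improvement to an exploratory analysis, not a defect that invalidates the study.

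**What to change.** Under Changes in Gut Microbiome–Related Metabolites and Gut Microbiome, add a partial Spearman correlation of symptom change with taxon or metabolite change, adjusted for:

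1. baseline nonmotor burden, for example the day-0 MDS-UPDRS part I score, which is already collected;
2. number of sessions received;
3. mean number of additional points per session, where session records allow.

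Report it beside the unadjusted value, label the unadjusted value descriptive, and rest any mechanistic reading on the adjusted one. Add the dependence of treatment content on symptoms to the limitations.

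The cost is about three degrees of freedom (58 falls to 55 with 60 patients), one or two derived variables, and some loss of power if the microbiome truly mediates a dose effect, as in the 86% to 75% example. Recruitment and observation have ended and analysis is under way, so this can be done on the existing data, except that the third covariate depends on what was recorded. No change to treatment is implied.
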